##### Facility-level covariates

Depending on data availability, we plan on examining several facility characteristics for descriptive purposes and to explore their association with the use of case review implementation strategies and completion rates. Following Glasgow et al.’s analytic framework of organizational factors, [31] indicators of two broad dimensions of organizational context will be examined: facility structure (e.g., number of annual primary care visits, patient clinical severity, facility complexity, region) and staffing/culture (e.g., primary care patient panel size, primary care staff ratio, number of mental health staff, specialty pain program workload, use of academic detailing for opioid safety, and several scales from the VA All Employee Survey) (Table 1). Facility structure variables refer to basic, unmodifiable structural characteristics, whereas staffing/culture variables include more modifiable characteristics that may affect the success of a facility’s QI efforts. All facility structure characteristics will be extracted from VA administrative data sources.

**Table 1 Tab1:** Definitions of facility characteristics planned for inclusion

Facility characteristic	Definition (data source)	Variable type
Facility structure		
Number of annual primary care visits	Total number of outpatient visits in primary care clinics (CDW)	Quartiles
Patient severity	VA calculates patient severity using a Nosos Risk Score, which is based on a risk adjustment model developed by Center for Medicaid & Medicare Services and further calibrated with VA pharmacy data, VA priority status, and VA-computed costs [41]. Scores are scaled such that the mean Nosos score = 1, so scores > 1 indicate greater-than-average cost and clinical complexity. (VA PACT Compass*)	Continuous, scaled by 0.10
Facility complexity	Based on an algorithm that takes into account patient risk, number and breadth of available specialists, intensive care unit availability, and teaching and research activities. (VA Office of Productivity, Efficiency, and Staffing)	1a, 1b, 1c, 2, or 3 (1a = most complex)
Region	Region of country defined by Census (HHS Area Resource File)	Northeast, Midwest, South, or West
Staffing/Culture		
Primary care patient panel size	Average panel size of primary care providers (VA PACT Compass*)	Continuous, scaled by 100

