Primary care staff ratio	Number of primary care support staff divided by the number of direct-care primary care providers (medical doctors or other direct-care providers such as nurse practitioners). Higher staff ratios indicate more support staff per direct-care provider, with 3 being the recommended minimum ratio for successful PACT implementation. (VA PACT Compass*)	Continuous
Mental health staff	Number of mental health full time equivalents relative to enrollees (Office of Mental Health and Suicide Prevention)	Continuous
Specialty pain program workload	Number of unique patients with at least one pain clinic visit (stop code 420) relative to enrollees (Office of Mental Health and Suicide Prevention)	Continuous
Academic detailing	Number of staff who undergo academic detailing on STORM, specifically, and other topics related to opioid risk management (SalesForce Database)	Continuous or categorical, as appropriate
Workgroup psychological safety	Degree to which employees agree that members of their workgroup are able to bring up problems and tough issues (1 = strongly disagree; 5 = strongly agree). Measured using a single item from the 2018 All Employee Survey.	Continuous
Servant leadership	Summary measure calculated from 5 items from the 2018 All Employee Survey assessing whether the work environment is a place where organizational goals are achieved by empowering others. Scores range from 0 to 100, with higher scores being more favorable.	Continuous
Raise and discuss ethics	Degree to which employees agree that their direct supervisor raises and discusses ethical concerns (i.e., uncertainty or conflict about the right thing to do) (1 = strongly disagree; 5 = strongly agree). Measured using a single item from the 2018 All Employee Survey.	Continuous
Workplace performance	“Workplace Performance” is a summary measure calculated using 6 items from the 2018 All Employee Survey that assess the degree to which the workplace environment has the right resources, training, goals, and innovation in place to support optimal performance. Scores range from 1 to 5, with higher scores being more favorable.	Continuous

*CDW* Corporate Data Warehouse, *DCG* Diagnostic Cost Group, *FY* fiscal year, *IOC* independent outpatient clinic, *VSSC* VA Support Service Center

*VA PACT Compass is an electronic dashboard of metrics that reflect the extent to which facilities are successful in providing team-based, continuous, and coordinated care

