##### Data collection

We will conduct the CFIR-based interviews with key informants from a purposeful sample of 40 facilities to understand the barriers and facilitators to implementation of the policy notice. These interviews will be conducted at the five VAMCs in each evaluation arm with the highest and lowest adherence to opioid therapy guidelines as measured by the Opioid Therapy Guideline (OTG) Adherence Report in the year prior to the release of the policy notice [33]. The OTG report contains a set of national metrics that examine facility-level performance on guideline-recommended opioid practices. Our team will recruit the policy notice POC at each facility (the same person contacted to complete the ERIC survey, or their replacement if the original POC is no longer in place) via email and/or telephone. If the current POC or an appropriate replacement is not available at a given VAMC, we will identify additional facilities in the order of their OTG adherence scores. Each facility POC will be asked to complete the interview and identify one or two additional individuals to be interviewed, based on who completed the most case reviews at that facility. The key informant plus the one or two individuals they recommend will form the interview sample at each facility, for a maximum of 120 telephone interviews. The 45-min interviews will be conducted via telephone by trained interviewers from the implementation evaluation team. Interviews will be audio-recorded and transcribed verbatim. While we considered having interviewees review their transcripts, research has shown that the errors that tend to get corrected are often minor, yet the process invites other methodological problems (e.g., interviewees changing their answers after the fact) [34]. Transcripts Interviewers will be blinded to randomization arm. The interviews will occur approximately 10–12 months after the policy notice release, which will provide separation from the ERIC survey in aim 1 (to reduce respondent burden) and allow us to identify how barriers and facilitators may differ after the risk thresholds are changed across randomization arms (*T*_1_ in Fig. 1).

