#### Aim 1b

The primary analysis for aim 1b will estimate the association between number of implementation strategies used and completion of case reviews at *T*_0_ + 6 months. If enough VAMCs meet the 97% target completion rate, we will analyze the data using logistic regression for the outcome of meeting the target rate; otherwise, we will model the proportion of case reviews completed. The outcome will be modeled using a generalized linear model with logit link and binomial family. This strategy will appropriately model the case review completion rates as being restricted between 0% and 100% and is equivalent to logistic regression for binary (yes/no) outcomes. For these analyses, the number of implementation strategies used will be the independent variable and will be coded as either continuous or categorical. Because difficulty in completing case reviews could increase as volume of very high-risk patients increases, we will include the number of very high-risk patients at each facility as a predictor along with the other facility variables.

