OMHSP is interested in understanding whether and how the case reviews of patients at very high risk of opioid-related SAEs get incorporated into practice and the factors that affect the ability of VAMCs to carry out such case reviews effectively. Understanding whether including facilitation (vs. no facilitation) in the policy notice increases facility compliance will inform future policy development. Testing the effect of adding new patients into the STORM risk group for whom case reviews are required will yield insights regarding which patients should be targeted for case reviews to achieve the desired reduction in opioid-related SAEs. The implementation evaluation will complement the analysis of changes in opioid-related SAEs over time and across randomization arms. We will be able to learn which implementation strategies are most effective in supporting case reviews, and how that relationship differs between the facilitation (which itself is an implementation strategy) and no facilitation arms. We will also be able to learn which barriers and facilitators, using CFIR, are most salient across the four arms. Finally, combining data on implementation strategies and barriers at such a large scale could advance implementation science by showing which strategies are naturally best suited to address certain barriers.

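### The primary aim 1b model omits the facilitation arm and, if the binary 97%-target outcome is used, carries too many facility covariates for about 80 facilities

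*Protocol article*

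**What the plan says.** Under Aim 1b, the primary analysis is to "estimate the association between number of implementation strategies used and completion of case reviews" at six months. The outcome is meeting the 97% target (logistic regression) if a sufficient number of facilities meet it, and otherwise the proportion of reviews completed (binomial family, logit link). On adjustment the section states that "we will include the number of very high-risk patients at each facility as a predictor along with the other facility variables". The facility variables are those of Table 1, titled "Definitions of facility characteristics planned for inclusion", which lists 13 characteristics. The text introducing the table is softer: "Depending on data availability, we plan on examining several facility characteristics for descriptive purposes and to explore their association".

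The facilitation arm is named neither in the primary model nor in Table 1. It enters aim 1b only in the later mediation analysis and in the wording of the power section and Table 3. The Discussion nevertheless says the evaluation will show which strategies work best and "how that relationship differs between the facilitation (which itself is an implementation strategy) and no facilitation arms".

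**The concern.** The protocol treats arm as a possible cause of both the exposure and the outcome. Aim 1a tests whether arm changes the number of strategies. The mediation analysis asks whether strategy count carries an effect of arm on completion. The power section words aim 1b as a difference in completion in the facilitation arm. If those hypotheses hold and arm is left out, the strategy coefficient picks up whatever arm does to completion by routes other than strategy count. The evaluation would then credit strategies with part of the effect of the notice wording.

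The second issue is model size. Logistic regression with very few events per slope gives odds ratios biased away from 1 and confidence intervals that are too narrow. The binary model is the first one the plan names, and strategies could be recommended for future policy rollouts on an inflated estimate.

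**Working it through.** **1. Reproduce the plan's figures.**
- Aim 1a: a two-sided t-test with SD 14 and the π/3 rank-test correction gives a detectable difference of 9.09 strategies at 80 facilities (stated 9.15), with 80.5% power at 9.15.
- Aim 1b: take the usual formula for one standardised continuous predictor, N = (z₀.₉₇₅ + z₀.₈₀)² / [P(1−P)(ln OR)²], with no other covariates. At P = 0.70 and OR 1.98 it gives 7.849 / (0.21 × 0.467) ≈ 80, and it returns about 70, 80 and 90 across all 15 cells of Table 3.
- Treated instead as a comparison of two arms of N/2 facilities, the same cells have only 19% to 28% power. Table 3 therefore matches a one-SD effect with no adjustment, although it is labelled as an arm difference. With an assumed R² of 0.3 or 0.5 between strategy count and the covariates, the detectable OR of 1.98 becomes 2.26 or 2.63.

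**2. Count the slopes.** From Table 1: visit quartiles 3, patient severity 1, complexity (five levels) 4, region (four levels) 3, nine staffing/culture variables 9 (academic detailing as one term). That is 20. Adding the number of very high-risk patients gives 21, and strategy count gives 22. With 80 facilities, 80 − 23 = 57 residual degrees of freedom remain.

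**3. Events per slope, binary outcome, 80 facilities** (events are the smaller outcome group).
- 50% meeting target: 40/22 = 1.8 (the maximum)
- 30%: 24/22 = 1.1
- 20%: 16/22 = 0.7

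**4. Effect on the binary estimate.** Logistic simulation with N = 80, a true OR of 1.98 per SD and 21 independent uninformative covariates:

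| Meeting target | Median OR, 22 slopes | SD of log OR | Coverage of 95% interval | Failed fits |
|---|---|---|---|---|
| 50% | 2.81 | 0.71 | 84.5% | 0.3% |
| 30% | 3.08 | 0.89 | 86.2% | 2% |
| 20% | 3.28 | 1.17 | 89.6% | 12% |

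A separate run put the median at about 2.8 to 3.4 over the same range. Strategy count alone gives medians of 1.99 to 2.04 with SD about 0.3, and a short covariate set gives about 2.1.

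**5. Effect of omitting arm.** With equal arms, the bias per strategy is approximately ln(OR_arm) × 0.25d / (196 + 0.25d²), where d is the between-arm difference in strategies and 196 = 14². This is a linear approximation with no true strategy effect.
- d = 9.15, direct arm OR 1.98: 0.683 × 2.2875 / 216.93 = 0.0072. Per 14 strategies, exp(0.101) = 1.11.
- d = 4.5, direct arm OR 1.5: 0.405 × 1.125 / 201.06 = 0.0023. Per 14 strategies, exp(0.032) = 1.03.
- d = 0: no bias.

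**6. Proportion outcome.** Assuming 50 reviews per facility, 70% completion and no strategy effect, omitting arm gives an OR of 1.10 to 1.11. With all 21 covariates kept, arm and prior guideline adherence added, and dispersion-scaled errors, the type I error is 5% to 6%.

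**7. Promised comparison.** The Discussion sentence is about how the strategy relationship differs by arm, which is effect modification. The aim 1b text names regressions without arm and a mediation analysis. Neither provides an arm-by-strategy-count term.

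**The case against.** **Arm is already handled in the mediation analysis.** Mediation regresses the outcome on strategy count and arm together, so an arm-adjusted coefficient will exist. This stands, but it is an additional analysis and does not correct the estimate declared primary.

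**The bias depends on assumptions.** The 9.15 strategies are a detectable difference, not an expected one. The documents give no direct arm effect, and Table 3's odds ratios, as labelled, would be total effects. Outreach to facilities below target began only as the survey closed, so at six months the arms differ only in notice wording. All of this stands, and it is why the bias is given as a conditional range. A reader might infer a larger bias from a direct arm OR of 4, but nothing in the documents supports that figure; the largest entry in Table 3 is 3.05.

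**The covariate list is hedged and the limit on power is conceded.** The list depends on data availability and is partly descriptive, and the Discussion admits limited power to control for all covariates. That makes 22 slopes the fullest reading. But the model statement says the variables will be included, and no rule for reducing them is given.

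**The model can still be fitted.** A reader might infer that it is close to non-estimable. At 30% attainment only about 1% to 2% of fits fail. Failure reaches 68% at 10% attainment, where the plan's fallback to the proportion outcome would be expected to apply.

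**Prior adherence and academic detailing.** A reader might call it an error to leave out guideline adherence "as measured by the Opioid Therapy Guideline (OTG) Adherence Report in the year prior to the release of the policy notice", or to adjust for "Number of staff who undergo academic detailing on STORM, specifically, and other topics related to opioid risk management". The first is a sensible baseline measure, but the documents do not link it to strategy count or completion, so its confounding cannot be sized. The second could reflect either implementation of the notice or general opioid-safety effort. Both are judgements.

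**A condensed article need not list every secondary term.** This is fair in general, but here a result is promised that no analysis described would produce.

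**Conclusion.** The point holds in two parts of different reach.

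First, arm should be in the primary aim 1b model whichever outcome is used. The bias from omitting it is moderate, about OR 1.03 to 1.11 per 14 strategies when the truth is 1. It arises only if arm shifts strategy count and also affects completion directly. The upper end borrows 1.98 from Table 3 as a direct effect, which is an assumption.

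Second, the covariate load is a problem for the binary outcome: at most 1.8 events per slope, a true OR of 1.98 estimated at about 2.8 to 3.4, and 95% intervals covering about 85% to 90%. These results assume 80 responding facilities, 20% to 50% meeting the target and independent covariates.

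The documents do not support saying that aim 1b as a whole is confounded and unstable. With the proportion outcome and dispersion-scaled errors, covariate count alone does no such damage.

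**What to change.** - Add the facilitation arm to the primary aim 1b model. It costs one degree of freedom.
- If the binary outcome is used, pre-specify a short adjustment set, for example arm, number of very high-risk patients, facility complexity as an ordinal term and pre-notice guideline adherence. With strategy count that is 5 slopes, or 24/5 = 4.8 events per slope at 30% attainment. Alternatively, use Firth penalised logistic regression. Put the other Table 1 variables in sensitivity analyses.
- Name the arm-by-strategy-count interaction as the secondary analysis that delivers the comparison promised in the Discussion.
- Show results with and without academic detailing as a sensitivity analysis.

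The cost is a change of wording; the added variables are already held. The downside is that some facility characteristics are no longer adjusted for in the primary model.

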Additional analyses will assess the association between the type of implementation strategies used and the case completion rate. We will assess the association between each individual strategy and case review completion in individual regression analyses. We will also assess the relationship between the percent of implementation strategies used within each cluster of strategy types and case review completion rates. Because we have adapted the ERIC survey for this evaluation, we will conduct confirmatory factor analyses to verify that the original clusters were maintained. If the factor analysis does not confirm the original clusters, we will describe the resulting strategy type factors and utilize summary scores based on the new factors. Finally, we will assess whether the overall number of implementation strategies used mediates the relationship between randomization arm and case review completion rate. We will test mediation using the bootstrapping methods of Preacher and Hayes [35]. These methods will allow for the direct estimation and testing of mediation and do not make any distributional assumptions (such as normality) regarding the variables or the test statistic. Analyses are based on taking a large number of bootstrap samples with replacement from the original data and estimating effects for each sample. The mean estimated effect and empiric confidence intervals are computed across all samples. Furthermore, because inferences do not depend upon large-sample theory, this method can be used for data with smaller sample sizes.

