##### Power and sample size

We computed power and sample size calculations using Pass 14 (Kaysville, UT). Based on the ERIC survey data from the HCV initiative [30], we anticipate receiving responses from at least 80 facilities and assume that the mean number of strategies implemented in the no facilitation arm will be 25 strategies with a standard deviation of 14. For aim 1a, we will have 80% power to detect a difference of 9.15 ERIC implementation strategies between the study arms using an alpha level of 0.05. Calculations are similar when allowing for different sample sizes with the ability to detect differences of 8.6 (90 facilities) to 9.75 (70 facilities) for varying facility responses. For aim 1b, the detectable difference in case review completion rates depends upon the sample size and the baseline completion rate in the no facilitation arm. Table 3 provides the difference in case review completion rates detectable in the facilitation arm for a variety of baseline completion rates and sample sizes. For example, assuming a 70% baseline completion rate and a sample size of 90, we have 80% power to detect an 11.6 percentage point difference in the case review completion rate in the facilitation arm, which is equivalent to an odds ratio of 1.91.

**Table 3 Tab3:** Power calculations for aim 1b

Baseline rate (%)	Sample size					
	70		80		90	
	∆* (%)	OR	∆* (%)	OR	∆* (%)	OR
50	+ 16.1	1.95	+ 15.2	1.87	+ 14.4	1.81
60	+ 14.8	1.98	+ 14.0	1.90	+ 13.3	1.83
70	+ 12.9	2.08	+ 12.2	1.98	+ 11.6	1.91
80	+ 10.2	2.31	+ 9.7	2.19	+ 9.3	2.09
90	+ 6.5	3.05	+ 6.2	2.84	+ 6.0	2.68

*Detectable difference from baseline case completion rate in the consequences (vs. no consequences) arm at a given sample size and with 80% power

#### Aim 2

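### The planned mediation test is justified on distributional grounds only, but the link from strategy count to case-review completion is not randomised, so facility-level confounding alone can produce a positive result

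*Protocol article*

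**What the plan says.** The last analysis described in the Aim 1b section of the Protocol article states that "we will assess whether the overall number of implementation strategies used mediates the relationship between randomization arm and case review completion rate". The method is the Preacher-Hayes bootstrap: facilities are resampled with replacement, and "The mean estimated effect and empiric confidence intervals are computed across all samples". The reason given is that "These methods will allow for the direct estimation and testing of mediation and do not make any distributional assumptions", and that inference does not rest on large-sample theory.

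Other sections bear on this:

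- **Aim 1b, primary analysis.** The link between number of strategies and completion is called an association. The model includes the number of very high-risk patients and the other facility variables. Completion is taken at T0 + 6 months.
- **Facility-level covariates.** Facility characteristics are to be examined for their association with both strategy use and completion rates.
- **Data analysis, Aim 1.** The primary strategy measure counts any strategy used in the past 6 to 8 months. Strategies adopted in direct response to the notice are a sensitivity analysis.
- **Trial status.** The notice was released in March 2018. The survey ran from 1 October to 16 December 2018.

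**The concern.** The indirect effect is a product of two links. The first, arm to strategy count, is protected by randomisation. The second, strategy count to completion given arm, is observational even with arm in the model. Staffing, leadership or earlier opioid-safety work could raise both the count and the completion rate, and the article itself expects facility traits to relate to both. In that case the second link is non-zero although strategies have no effect. If the arm also shifts the count, the interval for the product will tend to exclude zero.

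Freedom from normality assumptions does nothing about this. A reader told that the method directly estimates and tests mediation would take a positive result as evidence that the notice with facilitation worked by prompting more strategies. The data could show the same pattern if it did not.

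**Working it through.** **Inputs from the article (Power and sample size; ERIC instrument).** Facilities: "we anticipate receiving responses from at least 80 facilities". Strategy count: "the mean number of strategies implemented in the no facilitation arm will be 25 strategies with a standard deviation of 14". Detectable arm difference at 80 facilities: 9.15 strategies, 80% power, alpha 0.05. Correlation between strategy count and outcome in the earlier hepatitis C initiative: 0.43.

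**Assumptions.** 40 facilities per arm, two-sided 5%, 95% percentile interval, a linear completion outcome (a simplification of the planned logit model), no direct arm effect, true strategy effect zero. The residual correlation r between count and completion comes wholly from an unmeasured facility trait.

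**Step 1: reproduce the plan's figure.** The noncentral t test gives a detectable difference of 8.88 at N = 80. With rank-test efficiency 3/π it is 9.10, against the stated 9.15. At N = 70 and 90 the rank version gives 9.74 and 8.56, against 9.75 and 8.6. The aim 1a figures therefore reproduce for the planned Kruskal-Wallis test. The article gives no error rate for the mediation test.

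**Step 2: hand approximation.** The interval excludes zero roughly when both links are individually significant.

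- First link: z = shift / (14 × √(2/40)) = shift / 3.13. For 9.15, z = 2.92 and the chance of significance is Φ(2.92 − 1.99) ≈ 0.82. For 5, z = 1.60 and the chance is Φ(1.60 − 1.99) ≈ 0.35.
- Second link: t = r√77 / √(1 − r²). For r = 0.10, 0.20, 0.30 and 0.43, t = 0.88, 1.79, 2.76 and 4.18. The chances are about 0.13, 0.42, 0.78 and 0.99.

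**Step 3: bootstrap simulation beside the product of those chances.**

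| Confounded r | Shift 9.15: product | Shift 9.15: simulated | Shift 5: product | Shift 5: simulated |
|---|---|---|---|---|
| 0.10 | 11% | about 10% | 5% | about 6% |
| 0.20 | 35% | about 35% | 15% | about 15% |
| 0.30 | 64% | about 63% | 27% | about 27% |
| 0.43 | 81% | about 82% | 34% | about 34% |

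Repeat runs agree within a few percentage points. With r = 0, or with no shift, rejection is about 5% at most. The bootstrap therefore behaves properly when there is no confounding.

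**Step 4: effect of adjustment.** Take a shift of 9.15 and r = 0.43. If covariates remove 25%, 50%, 75% or 100% of that correlation, rejection falls from 81% to 68%, 40%, 14% and 4%.

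**Step 5: order in time.** Read as six months after a March 2018 release, the outcome falls in about September 2018. The survey asks about the 6 to 8 months before a response given between October and mid-December. The count can thus include strategies adopted up to about three months after the outcome, some perhaps because of it.

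**The case against.** Four points on the other side deserve weight.

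- **Planned covariates.** The primary aim 1b model already includes patient volume and facility variables, and Table 1 covers staffing, leadership and academic detailing. The mediation sits under the same aim. This stands in part: Step 4 shows that adjustment helps, but nearly all the confounding must be removed. The article does not say that these covariates enter the mediation equations, a detail it may leave to a fuller plan. Its Discussion concedes limited power to control for all relevant covariates.
- **Omission.** Sensitivity analyses are commonly left to an analysis plan. True, and their absence alone would not be a finding. The point here is what is stated: a claim to test mediation directly, supported by properties that cannot support it.
- **Low stakes.** This is an additional analysis, and the primary one is called an association. That stands and limits the weight of the point.
- **Size.** The 0.43 comes from another initiative with another outcome, and nothing says that any of it is confounded. The 9.15 is a detectable difference, not an expected one. Both stand, so only a range can be given.

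A reader might infer more than the article supports. The bootstrap does not test a wrong null; without confounding its error rate is about nominal or lower. Nor is 82% the false-positive rate of this trial or a ceiling: with the same r, a shift of 14 at N = 80 gives 97%, and a shift of 9.15 at N = 141 gives 98%. Finally, the mediator is the overall count, so a false result could not show which strategies to promote. The Discussion's statement "We will be able to learn which implementation strategies are most effective in supporting case reviews" fits the separate per-strategy and per-cluster regressions.

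**Conclusion.** The point holds as a limitation of an additional analysis that the wording hides. As described, the mediation test can return a positive result when strategies have no effect on completion. The source is confounding of the unrandomised link, with possible reverse ordering in time; it is neither the bootstrap nor the use of a product.

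The size depends on how far the arm shifts the count, how much residual correlation is confounded, how many facilities respond and how well covariates remove the confounding. At 80 facilities without adjustment, the confounded scenarios shown run from about 6% to 82%. The share of any correlation that is confounded cannot be learned from the article. A cheap correction is worth making; the primary aim 1b analysis is not called into question.

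**What to change.** Keep the bootstrap and make three changes in the Aim 1b mediation text.

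1. Put the same covariates in both the mediator and the outcome equation: the Table 1 facility characteristics, as measured before the notice, and the number of very high-risk patients.
2. Report the residual mediator-outcome correlation at which the indirect effect, and its nearer interval limit, reach zero. Present it for the reader to judge, without a pass/fail benchmark; the documents give no basis for one.
3. Replace the claim of direct estimation and testing with wording that names the assumption: no unmeasured confounding of strategy count and completion given arm and covariates. Report an indirect association unless that assumption is defended. State the timing limit beside it.

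Cost: a little more analysis on data already planned for collection, some wording, and a weaker mediation conclusion. Table 1 in full takes about 20 degrees of freedom (3 for visit quartiles, 1 for severity, 4 for complexity, 3 for region, 9 for staffing and culture if all are single terms), and patient volume makes 21. With about 80 facilities, a short list may have to be fixed before the outcome data are examined.
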